## Abstract

**Background:**

A limited amount of research has examined the effect of changing public open spaces on active living. This paper will present the study protocol of a community-based intervention study co-designed in an interdisciplinary collaboration with community members to develop urban installations highly tailored to promote active living among children (10–13-years-old) and seniors (>60-years-old) in a deprived neighbourhood in Copenhagen.

**Methods:**

The study builds on a quasi-experimental study design with two sub-studies: 1) a children study and 2) a senior study. The interventions will be developed, designed and implemented in collaboration with local children and seniors, respectively, using different co-design tools and methods. We will evaluate the effect of the interventions on children’s and senior’s use of the new-built urban installations using accelerometers in combination with GPS as well as systematic observation using the System for Observing Play and Recreation in Communities (SOPARC). A process evaluation with focus groups consisting of the various stakeholders in the two sub-studies will be used to gain knowledge of the intervention processes.

**Discussion:**

The paper presents new approaches in the field of public open space interventions through interdisciplinary collaboration, participatory co-design approach and combination of measurements. Using both effect and process evaluations the study will provide unique insights in the role and importance of the interdisciplinary collaboration, participatory processes, and tailoring changes in public open space to local needs and wishes. These results can be used to guide urban renewal projects in deprived neighbourhoods in the future.

**Trial registration:**

Retrospectively registered with study ID ISRCTN50036837. Date of registration: 16 December 2016.

## Background

Promotion of more active living in the last decade has become an important strategy to reduce the effect of increasingly sedentary lifestyles [1] that are responsible for more than 5 million deaths per year world-wide [2]. Active living is a way of life that reduces sedentary behavior (SB) and integrates more physical activity (PA) into daily routines. Active living includes things such as walking or cycling for transport; exercise or play for pleasure and fitness; sitting less during work or school hours; or sitting less at home [1]. Active living is associated with a multitude of positive short- and long-term health consequences due to its stimulating influence on physical, mental and social health [3–5].

How physically active people are in their daily life is related to many individual factors such as age, sex, socio-economic status (SES), but also on the characteristics of the physical environment they live in [6, 7]. It is documented that people with a low SES on average are less physically active compared to people with a high SES. This disparity in active living is aggravated when people live in neighbourhoods with low walkability [8]. The characteristics of public open space in the local neighbourhood are most important for those people that typically have the lowest mobility and are most sensitive to safety issues: children and elderly [9]. These two age groups are also relevant from a health perspective. Children’s low PA levels are worrying since PA patterns in early life are likely to track into adulthood [10] whereas older adults are the least physically active of any age group and generate the highest expenditures for medical care [11, 12].

The role of public open space in promoting active living has received increased attention in the past decade, but knowledge on how to improve public open space to increase active living is scarce and has been asked for [13, 14], in particular, to reduce social inequality in health [15, 16]. There are many reasons for this limited knowledge. First of all, developing and implementing changes in public open space is complex, expensive and takes time [17]. Second, creating changes that could have the desired effect requires involvement of many different participants (e.g., architects, planners, and public health professionals) traditionally not working together [14, 18]. Third, evaluating the effect of such changes requires an innovative study design and a wide range of methods [19, 20]. From a research perspective, we pose that neither of these challenges can be addressed satisfyingly by involving researchers from only one field.

To address these issues we developed the ‘Move the neighborhood’ study. The objective of this study is to collect research based knowledge on how to alter public open space in a deprived neighbourhood in Copenhagen to promote active living among people living there. Our target groups are children (10–13-years-old) and seniors (>60-years-old) living in the neighbourhood. In an interdisciplinary collaboration we developed a quasi-experimental intervention study that was inspired by the principles of Community-Based Participatory Research (CBPR) [21]. We use a co-design approach to develop highly tailored interventions in the form of urban installations [22].

### Aim

This paper will present the study protocol of the ‘Move the neighborhood’ study including a description of the case, co-design based development and implementation of urban installations, and measurements to be used in the evaluation of the study.

### Study design

The study is a quasi-experimental community-based intervention study including two sub-studies: 1) a children study and 2) a senior study. Each of the two sub-studies is divided into three phases: 1) pre-intervention; 2) intervention; 3) post-intervention. The intervention phase includes different interlinked co-design steps: understanding, developing and implementing. Information collected during the first co-design step, understanding, will be used to start the second co-design step, developing. In this step researchers and participants will in an iterative process jointly explore and develop ideas where e.g. participant ideas will be visualised by designers and then presented back to participants to improve and decide upon. The ideas will be interpreted and implemented in the final step. The evaluation of the study is separated into an effect evaluation and a process evaluation. The effect evaluation will be conducted pre-intervention (baseline) and post-intervention (follow-up) to assess the effect of the interventions whereas the process evaluation will be conducted before, during and after the intervention phase to describe how the interventions were developed and implemented. To be able to support a comprehensive evaluation of the study, a range of qualitative and quantitative methods will be employed. The study design with its two sub-studies and phases is illustrated in Fig. 1.

**Fig. 1 Fig1:**
[figure not shown]
Illustration of study design

### The neighbourhood

The intervention study takes place in the neighborhood of Sydhavn [the South Harbour] in Copenhagen, Denmark. The neighbourhood has 10,276 inhabitants [23], spans an area of 1.2 km^2^ and is framed by high-traffic corridors [24].

The district was planned and built between 1908 and 1950 in line with the welfare planning ideologies of that time in an effort to provide healthier and better living conditions for the growing work force moving into Copenhagen. With reference to the English garden cities the neighbourhood consists of homogenous 2–3 story brick buildings arranged in geometrical structures punctuated by green boulevards, small parks and public squares [23, 25]. Because of a decline in the number of inhabitants throughout the years the neighbourhood has become a place where socially challenged people are housed by public authorities [23]. Demographically the area is one of Copenhagen most disadvantaged neighborhoods. In this neighbourhood 22.1% of the population stands outside the labour market (17.1% on average in Copenhagen), 32.0% has no formal education (21.3% on average), and 40.2% has a low income (30.6% on average) [23]. With 73.0 years as average life expectancy, the neighbourhood has one of the lowest average life expectancies in Denmark where the average is 80.6 years [26].

As one of the last remaining deprived districts in Copenhagen that has not been subject to urban renewal, the area is selected to undergo large changes in the coming years through a municipal renewal initiative. Copenhagen Municipality will focus their investments in the neighbourhood on renewing urban green spaces, opening a Metro (subway) line in 2022, and a large park renewal project focusing on storm water management [23]. The public open space interventions planned in this study tie into this process, which allows for a close linkage between our intervention study and the municipal urban renewal strategies.

A map of the neighbourhood showing the different intervention sites is presented in Fig. 2.

**Fig. 2 Fig2:**
[figure not shown]
A map of the neighborhood

### Iterative co-design intervention process

Throughout the three-step intervention phase we will use a community engaging approach called co-design that is increasingly used in urban development projects [27]. Co-design is a partnership approach that engages community members and designers in a joint design and implementation process [27]. In current study the community members are local children and seniors and the designers are researchers with professional backgrounds in design, architecture and landscape architecture who are part of the research team. The aim is to design and build urban installations in public open spaces that form new destinations in the neighbourhood that can support and increase movement, play, social interaction, quality of life and health for the community members through a process of designing *with* the users and not *for* them [27]. Co-design is a social process, with significant creative potential for innovation, which can be actively exploited when engaging community members in the design and construction process in public open spaces [28]. Various local key stakeholders, such as craft and design teachers, leader of the youth club, carpenters, members of a local government organisation called the Areal Renewal Office, social service managers and administrators at the two housing areas, have been identified and will be involved in study-related activities and meetings throughout the co-design intervention process. The stakeholders will be important in supporting the permitting of green space interventions and in the recruitment of participants [29]. The local stakeholders will be the link between the community members (children and seniors) and co-design researchers. The two sub-studies will be tailored to the two target groups, which will be elaborated on in the following.

#### Co-designing with children

In the children study, local children will be engaged throughout all intervention phases [30]. As part of the understanding phase, a pilot study was conducted in August 2016 at a local children’s culture festival to test and develop different co-design tools, such as mappings, creating collages, and building full-size prototypes in the public green space. The purpose of the pilot study was to gain insights into the children’s perceptions and experiences of their neighborhood [31, 32], to test co-design tools and to mobilise stakeholders by making the project visible in the community.

The development phase will contain workshops in two parallel processes where designers together with local children will use different co-design tools and methods from design practice to bring together insights and ideation in an iterative design process using mapping, collage-making, site explorations, sketching, and model making to design urban installations [33, 34]. One co-design process takes place at the local public school and includes two grade 5 classes (11–12-years-old, *n* = 39) during their craft and design classes, one day a week from January to May 2017. The second co-design process takes place in a local youth club among 10–13-years-old children (*n* = 20). The process will consist of workshops conducted in the youth club scheduled to take place once a week over a period of five weeks during spring 2017.

The implementation of interventions will also take place in collaboration with children, designers, and creators experienced in the execution of urban installations. Two locations are selected as intervention sites. The selection criteria were their immediate proximity to child oriented cultural public institutions (cultural house, school and youth club) and that they were embedded in accessible green spaces that already had spatial qualities that could serve as physical frames for the interventions (see the two sites on the map, Fig. 2). Approximately 110,000 USD is allocated to construct 2–3 urban installations targeting children.

#### Co-designing with seniors

In the senior study, local seniors will be engaged throughout all intervention stages. In the understanding phase lasting from September 2016 to March 2017 ethnographic fieldwork [35] in combination with individual go-along interviews using a GoPro camera in the neighbourhood (*n* = 16) [36–38] and a photo elicitation project (*n* = 20) [39] was carried out among seniors (>60 years old) living in two social housing areas. The participating seniors were recruited with help from the social staff working in each of the social housing areas. In order to gain knowledge with a wide perspective, we invited participants with an equal ratio of men/women and with different age-related impairments. These initial data serve a dual purpose by firstly making it possible to gain insights into the senior residents’ everyday life and e.g., identify perceived barriers and potentials for using their public open space, and secondly, by providing a visual dimension to the interviews that potentially can be part of the following co-design workshops [40–42]. Engaging the participants in the early stages of identifying barriers and potentials in their local neighbourhood will be the first step in preparing their mind-sets for the co-design process and will underline the importance of their input to the project. All participants will be invited to take part in the following design and development workshops along with other interested senior residents from the two social housing areas. This approach makes it possible to create a co-design process that provides a tailored perspective targeting the specific physical and social context.

The development process will consist of three workshops in each of the two social housing areas scheduled to take place every two to three weeks during a six to eight week period in April–May 2017. Different co-design tools and methods from design practice, such as mapping, making collages and building prototypes will be used to bring together insights and ideation in an iterative design process. Ideally, the co-design process will involve the same 20–30 seniors throughout the series of workshops, representing the two social housing areas in an equal ratio.

The open spaces within the two social housing areas have been selected as sites for the interventions (see the two sites on the map, Fig. 2). Given the potentially low physical abilities of the senior residents the implementation of the urban installations will be carried out by professionals, but the senior residents will be invited to participate in the construction based on their individual interests and capabilities. Approximately 110,000 USD is allocated to construct 2–3 urban installations targeting seniors.

### Evaluation measurements

As described above, the study consists of an effect evaluation and a process evaluation that each has their own data collection methods and measures, described in more detail below.

#### Effect evaluation

The aim of the effect evaluation is to examine the use of the urban installations developed and implemented with and for children and seniors. The System for Observing Play and Recreation in Communities (SOPARC) was used to systematically observe the use of selected locations in the pre-intervention phase (September–October 2016 and April–May 2017) and observations will take place in the post-intervention phase to systematically observe the use of the new urban installations and surrounding locations (September–October 2017 and April–May 2018). SOPARC is a validated tool to assess the use of public spaces in community settings [43]. SOPARC is used to record gender, age, PA level, primary activity and social interactions for each observed person. The compiled SOPARC data makes it possible to determine the number of users at different times and days of the week, as well as assess user characteristics, activity levels and common activities carried out by users at the observation locations. Furthermore, at the beginning of each observation, weather conditions were recorded and a picture was taken to visualise each area and its features. Observations take place at each of the four intervention sites (see Fig. 2) during three weekdays and one weekend day, four times a day (morning: 7.30–8.30, lunch: 11.30–12.30, afternoon: 15.30–16.30, and evening: 19.30–20.30). SOPARC data was collected over a five-week period by four trained observers and resulted in a total of 64 h of observations. SOPARC baseline data will be used to qualify the co-design workshops in the intervention process of the two sub-studies.

In the pre- and post intervention phase accelerometers and GPS are used to assess where participants spend their time and how physically active they are at those locations. For the children study, the ActiGraph accelerometer model GT3X+ is used to objectively measure PA with a 15 s epoch, and the QStarz BT-Q1000xt GPS device is used to record their location every 15 s. The GT3X+ is recognised as a valid and reliable tool for measuring children’s PA levels [44], and the Qstarz GPS device has shown good dynamic accuracy for recording locations [45]. The children are asked to wear the accelerometer and GPS in an adjustable elastic belt on their waist. For the senior study, two AXIVITY accelerometers model AX3 are used per person to objectively record PA and SB (raw data, 50 Hz). The AX3 device provides acceptable validity for measuring PA in seniors [46, 47]. The AX3 accelerometers are taped to the skin, one on the lower back and one on the thigh. We have chosen two skin taped AX3 devices for the senior study as they are more suitable than the ActiGraph used in the children study to identify SB (e.g. standing or sitting), which we expect will be the main behavior amongst seniors. The same Qstarz GPS device is used to measure the participating senior’s location every 15 s. The participating seniors are given several choices on how to wear the GPS device (on a belt, in an ankle holder, or on lanyard). All participating children and seniors are asked to wear the equipment for seven consecutive days, and only to take the GPS off when there is a risk of contact with water and at night when it is charging. To increase compliance the participants received short reminder text-messages on their mobile phones twice a day. For the baseline measurements 80 children and 37 seniors were recruited to wear accelerometers and GPS. The children were recruited through the local school. The seniors were recruited through local stakeholders who know the senior residents (i.e., social service managers at the two social housing areas) and by participating in their social activities in the neighbourhood.

During baseline data collection all participating children also completed an electronic questionnaire asking for background information and PA behavior during and after school hours. Participating seniors were interviewed in their homes, and the interviewers used an electronic questionnaire to ask about background information and barriers towards using their neighborhood. VERITAS, an interactive online map-based questionnaire, was used by the interviewers to identify daily mobility and social interactions [48].

#### Process evaluation

The aim of the process evaluation is to evaluate how the intervention has been implemented [49]. In the pre- and post-intervention phase focus group interviews will be conducted with participants that are part of the intervention process (local children and seniors, designers, creators), as well as local stakeholders (craft and design teachers, leader of the youth club, members of the Areal Renewal Office, social service managers and administrators at the two housing areas). Ideally the focus groups will include the same persons from each group (*n* = 4–8) before and after the intervention and will be conducted separately to give interviewees the possibility to speak freely. In total, four or five focus group interviews will be conducted before and after the intervention in each of the two sub-studies. The first focus group interview will focus on the different experienced challenges before the intervention, and the expectations for the coming development and implementation process. The second focus group interview will provide insights into the development and implementation process, experienced acceptability, appreciation and appropriation of the interventions. The focus groups will be conducted locally and will be audio-recoded. During the intervention phase participant observations will be conducted during workshops to gain an understanding of the context and intervention explored. This information will help guide the post-intervention focus group interviews [49].

### Data analysis

#### Effect evaluation analysis

SOPARC data will provide information on how specific places are been used and by whom, before and after the interventions, as well as the specific use of the implemented urban installations. For each observed area the total number of users will be compared, as will the share of children and seniors, the average activity level, and common activities.

The collected GPS and accelerometer data will be merged and processed using the Personal Activity and Location Measurement System (PALMS, https://ucsd-palms-project.wikispaces.com) to match the two types of data based on their timestamp, remove GPS error, classify accelerometer data into activity levels, and detect walking, cycling and vehicle trips. The combined accelerometer and GPS data will be further processed in a PostgreSQL database were GIS (geographic information system) data on all intervention sites, green spaces, and daily destinations will be incorporated as well. This will make it possible to assess which areas and destinations participants visited, how often they did this and how long they stayed. It will furthermore be possible to assess how active participants were during their visit to a location, and which mode of transportation they used to get there (see *Klinker* et al. 2014 for more information on this method) [50]. The differences between baseline and follow-up data will be analysed as repeated cross-sectional measures comparing the number of users, the share of children, the share of seniors, as well as average activity levels.

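### The listed effect measures (all-age totals, shares, average activity not stated by age) can fall when more children or seniors use a site actively, and would be confounded by recruitment if applied to device data

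*Protocol article*

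**What the plan says.** Under Evaluation measurements, Effect evaluation, the purpose is put in terms of two groups: "The aim of the effect evaluation is to examine the use of the urban installations developed and implemented with and for children and seniors".

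Under Data analysis, Effect evaluation analysis, the measures are listed twice. The paragraph on SOPARC sets user totals per area against each other, "as will the share of children and seniors, the average activity level, and common activities". The paragraph on GPS and accelerometer data ends with the treatment of baseline and follow-up differences: "analysed as repeated cross-sectional measures comparing the number of users, the share of children, the share of seniors, as well as average activity levels".

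Neither list names the number of child users or the number of senior users. Neither says that activity will be averaged within age group.

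On the device sample, the Effect evaluation section reports: "For the baseline measurements 80 children and 37 seniors were recruited to wear accelerometers and GPS". It adds: "The children were recruited through the local school"; seniors came through local stakeholders and social activities. In explaining the choice of accelerometer, the same section expects sedentary behaviour to dominate among seniors: "standing or sitting), which we expect will be the main behavior amongst seniors".

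**The concern.** The aim concerns children and seniors, so the direct measures are how many of each use the sites and how many of those are active. The listed measures answer other questions. A share has all users in its denominator, so it reacts to adults and teenagers as much as to the target group, and the child and senior shares compete with each other. An activity average over all ages is weighted by composition. If an installation attracts people who are less active than those already there, the average falls although nobody moves less. The protocol's own expectation about seniors makes this a realistic outcome at a senior site.

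The device data raise a second problem. Children and seniors were recruited separately, and the number wearing devices can differ between waves. A count of users, or a child or senior share, taken from that sample mixes use of the sites with recruitment.

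At stake is interpretation. Several measures that can point in opposite directions are listed side by side, and none of them is tied directly to target-group use.

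**Working it through.** **Inputs from the protocol.** 80 children and 37 seniors with devices at baseline. SOPARC records age and activity level for each observed person. Observation schedule: four sites, four days, four one-hour slots. No sample size, power or effect size is stated, and none is needed here. All other counts and rates below are assumptions chosen to show direction.

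**Check of the stated observation time.** 4 sites × 4 days × 4 slots × 1 h = 64 h, which agrees with the 64 h reported. A per-hour denominator is therefore available.

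**1. Shares.** With T target-group users among N users, T/N falls whenever T1/T0 < N1/N0.

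| Assumed change | Target-group count | Share |
|---|---|---|
| 10 children of 40 users to 20 of 100 | doubles | 25% to 20% |
| Children/seniors/others 40/20/40 to 60/30/110 | both up 50% | children 40% to 30%; seniors 20% to 15% |
| 40/20/40 to 80/20/40 | seniors unchanged | seniors 20/100 = 20% to 20/140 = 14.3% |

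The counts can be recovered from the planned output: 40 × 25% = 10 and 100 × 20% = 20.

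**2. Activity averaged over all ages.** Assume 80 non-seniors, 70% active, and 20 seniors, 30% active.

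- Start: (80 × 0.70 + 20 × 0.30)/100 = 62/100 = 62.0%; active seniors = 6.
- Seniors rise to 60, same rates: (56 + 18)/140 = 74/140 = 52.9%; active seniors = 18.
- Seniors rise to 60 and 40% are active: (56 + 24)/140 = 80/140 = 57.1%; active seniors = 24.

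In the last case there are three times as many seniors, each group is at least as active as before, and active persons rise from 62 to 80. The average still falls by 4.9 points.

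**3. What the listed measures cannot give.** Take a total of 100, a senior share of 20% and a pooled active proportion of 62%. There are then 20 seniors and 62 active people. Because the 80 non-seniors could account for all 62, the number of active seniors can be anything from 0 to 20. Total, share and pooled average together do not determine it.

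**4. Device data, if the closing sentence applies to them.**

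- Child share of wearers at baseline: 80/(80 + 37) = 80/117 = 68.4%.
- No change in behaviour, 70% of children and all seniors at follow-up: 56/(56 + 37) = 60.2%.
- No change in behaviour, all children and 40% of seniors: 80/(80 + 14.8) = 84.4%.
- Child visitors at a constant 20% visit rate: 80 × 0.20 = 16 at baseline, 56 × 0.20 = 11.2 if 70% return. The number of users falls with no change in use.
- Share among visitors, rates doubling in both groups from 20% to 40%: 16/(16 + 7.4) = 68.4% and 32/(32 + 14.8) = 68.4%. The doubling leaves no trace in the share.
- Share among visitors, 40% of children and 20% of seniors visiting: 32/(32 + 7.4) = 81.2%. Among visitors, then, the share reflects both recruitment and relative visit rates.

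**The case against.** For SOPARC, the total is compared next to the shares, so the doubling in the 10-of-40 example is visible to anyone who multiplies. A reader might infer that target-group counts are lost; they are not, only unnamed. A reader might also infer that a successful installation would be reported as a failure. The protocol has no decision rule under which a falling share or average counts against the intervention, so that does not follow. Both replies stand, but neither reaches the number of active children or seniors.

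The article does not say that the activity average is pooled, and stratification may be left to a fuller plan. That is fair: the point is that the measure as listed permits a pooled reading. The remark on seniors' sedentary behaviour justifies the device choice and does not forecast activity at the sites, so it supports plausibility only.

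On devices, it is tempting to say that the shares are set by recruitment. That is too strong. The closing sentence repeats the SOPARC list and may have been meant for SOPARC alone, or for the share of participating children or seniors who visit a site. Nothing states that the two sub-studies are pooled, and among visitors the share also depends on visit rates. The same paragraph already says that visits, their frequency and duration, and activity at each location can be assessed. What remains is that the sentence, where it stands, is not limited to SOPARC, and that read as covering device data it compares quantities confounded by recruitment.

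Finally, the Background states the objective for people living in the neighbourhood, so all-age totals are relevant and should stay.

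**Conclusion.** The concern holds in a limited form. Shares, and an activity average not taken within age group, are named as baseline-to-follow-up comparisons, and both can move opposite to target-group use. That is arithmetic and does not depend on the assumed counts. The size does: the examples give falls of 5 to 10 points in a share, and of 4.9 to 9.1 points in pooled activity, while target-group use and the number of active people rise. The lasting gap is that active children and active seniors cannot be derived from the listed measures.

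For device data the point is conditional on how the closing sentence is read. If it applies, the child share of wearers could range from 60.2% to 84.4% with no change in use, under assumed retention of 70–100% for children and 40–100% for seniors. This is an inexpensive improvement to make before follow-up data are analysed; it is not a flaw that invalidates the evaluation.

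**What to change.** **SOPARC.** Name as effect measures, for children and for seniors separately, (a) the number of users per observed hour, in the SOPARC age categories, and (b) the number of those who are physically active per observed hour. Report activity level within age group. Keep shares as description and all-age totals as a supporting measure.

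**Device data.** Say whether the closing sentence of Effect evaluation analysis covers them, and state that child and senior shares are not compared there. Within each sub-study, use the proportion of valid wearers who visit a site and the time spent at the site per valid wear-day, counting non-visitors as zero.

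**Cost.** Wording and tabulation only. SOPARC already records age and activity per person, and the device data already yield visits and duration. One downside is that age-specific counts rest on age judged by observers, which the Measurements part of the Discussion admits is difficult. The planned shares rest on it equally. The article does not give the SOPARC age categories, so they may not match 10–13 years and over 60 exactly; the categories used should be stated.
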